#### **7.1.3 Stable Disease**

Insufficient change to qualify for Partial Response or Progressive disease.

#### **7.1.4 Progressive Disease**

At least a 25% increase in the longest diameter on an axial image of any enhancing tumor that is  $> 1\text{ cm}$  in each of 2 perpendicular planes on consecutive CT or MRI images or the appearance of a new radiographically demonstrable lesion that measures  $1\text{ cm}$  or greater in each of two perpendicular axial planes taking as a reference the first post-operative or first post-radiation scan whichever is most recent.

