### **3.15 Rationale for Current Study**

We have demonstrated in murine models that the vaccination with a tumor-specific peptide, PEPvIII-KLH (now known as CDX-110), can induce humoral and cellular immune responses and increase survival. Our Phase I and multi-institutional Phase II human studies demonstrate that vaccinations with an EGFRvIII-specific peptide induced T- and B-cell immunity, produce complete radiographic responses in all patients with residual tumor, and universally eliminate EGFRvIII-expressing cells (Heimberger, Hussain et al. 2006; Heimberger, Hussain et al. 2006). Recurrent tumors, however, continue to express wild-type EGFR suggesting that the immune response is specific, but productive intra-molecular cross-priming does not occur. We believe that cross-priming may be hindered by the presence of TRegs.

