## **7 CLINICAL RESPONSE EVALUATIONS AND STATISTICS**

### **7.1 Radiographic Response and Progression Criteria for Patients with Residual Disease**

Residual disease will be defined as contiguous contrast enhancement  $> 1\text{ cm} \times 1\text{ cm}$  in each of two perpendicular planes. For residual disease present at the time of the last MRI prior to initiating vaccine treatment, radiographic response will be evaluated based on the NCI-endorsed, World Health Organization RECIST criteria and using a modified version of the MacDonald criteria (Macdonald, Cascino et al. 1990; Galanis, Buckner et al. 2006) which is outlined below.

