#### **7.1.2 Partial Response**

At least a 30% reduction in longest diameter on an axial image of any enhancing tumor on consecutive CT or MRI images at least 1 month apart, and neurologically stable or improved and at the same or a lower steroid dose. To be assigned a status of “Partial Response” as a best overall response, changes in tumor measurements must be confirmed by repeat assessments that should be performed no less than 4 weeks after the criteria for response is first met taking as a reference the first post-radiation scan.

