## **7.2 Special Circumstances**

- **If a scan is suspicious but not definitive for progressive disease (including indeterminate lesion size or enhancement that is not clearly disease progression) in the absence of clinical progression, an investigator may elect to confirm progression through alternate means, including PET scan, biopsy, repeat MRI at 4 weeks, symptomatic follow up or other modalities.**
  - Protocol treatment will continue until the investigator considers progression documented.
- **Disease that was measurable at baseline and appeared to be one solid mass splits to become 2 or more smaller lesions**
  - note that the lesion has split, to identify the separate lesions as unique and to record the measurements of each.
  - appearance of these individual split lesions will not automate a response assignment of PD; they will contribute to a determination of progression only if the sum of all lesions meets the criteria for PD.
- **2 or more lesions which were distinctly separate at baseline become confluent at subsequent visits**
  - note the occurrence and capture the required measurement(s) of the confluent mass.
- **A required region of a baseline scan may be unavailable or technically inadequate, and 1 or more lesions are detected on a subsequent scans.**
  - Such lesions are identified as additional evaluable lesions that do not contribute to determination of that visit's response.
  - If at a successive time point disease progression is noted, the overall response per time point will be PD.
  - For those areas inadequate at baseline, the first scan available will become the reference scan by which later scans are compared for evaluable progression.
- **1 or more lesions are detected in regions unavailable or inadequate at baseline that were also not required**
  - regarded as new lesions, resulting in an overall response of PD for that time point.
- **Regions are not available or adequate at post-baseline visit assessments that showed disease at baseline**
  - an overall response of NA will be assigned to that visit unless other available data shows progression.

| Overall Response | Measurable Lesions                                                                    | Evaluable Lesions | New Lesions | Overall neurological status             | Steroid Use               | Additional notes                                                                                                 |

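### The size criterion for progression in 7.1.4 stays tied to a fixed pre-vaccine scan, so regrowth alone after a response does not meet it until 125% of the reference diameter

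*Protocol*

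**What the plan says.** Section 7.1.4 has two radiographic routes to progressive disease. The size route is "At least a 25% increase in the longest diameter on an axial image of any enhancing tumor that is" larger than 1 cm in each of two perpendicular planes. The other is "or the appearance of a new radiographically demonstrable lesion that measures" at least 1 cm in each of two planes. The reference is set by "taking as a reference the first post-operative or first post-radiation scan whichever is most recent". The flow sheet (section 11) places the post-radiation MRI before immunization #1.

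Section 7.1.2 defines partial response as "At least a 30% reduction in longest diameter on an axial image of any enhancing tumor", "taking as a reference the first post-radiation scan". Section 7.1.3 makes stable disease whatever is neither partial response nor progression. Section 7.1 names its basis as "RECIST criteria and using a modified version of the MacDonald criteria", in the form it then sets out, and applies it to residual enhancement larger than 1 cm × 1 cm.

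The only other reference rule, in 7.2 for regions inadequately imaged at baseline, is also a fixed first scan: "the first scan available will become the reference scan by which later scans are compared for evaluable progression". No rule in 7.1, 7.2 or 7.3 refers progression to the smallest tumour since baseline.

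**The concern.** With a fixed reference, the amount of regrowth needed to meet the size criterion rises with the depth of the earlier response. Progression by size is thus dated later in responders than in patients whose tumour never shrank, even if both tumours are growing at the same rate.

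The protocol gives reason to expect this situation. Section 3.15 says that vaccination in earlier studies did "produce complete radiographic responses in all patients with residual tumor". Those were complete responses, and here the text is silent on a basic question: does enhancement returning at the same site count as a new lesion or as regrowth of the old one? Two readers could date the same progression differently.

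TTP is put to use. Progression-free survival against historical cohorts is a secondary objective (2.2.2). Section 10.3 compares TTP between the arms and with historical controls by Cox model. It makes further interest in daclizumab conditional on no significant reduction in TTP or overall survival. A rule that delays progression only in responders could turn a difference in transient shrinkage into a difference in TTP.

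**Working it through.** The plan states no figure to reproduce, so the check is arithmetic on its own thresholds.

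**Inputs.** Progression by size: 25% increase in longest diameter over the reference scan (7.1.4). Partial response: 30% reduction from the post-radiation scan (7.1.2). Let D0 be the reference diameter and s the fractional shrinkage to the smallest size, (1 − s) × D0.

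**Formulas.**
- Size threshold as written: 1.25 × D0.
- Regrowth needed from the smallest size: 1.25 / (1 − s).
- Threshold if measured from the smallest size: 1.25 × (1 − s) × D0.

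| Shrinkage s | Regrowth needed in diameter, as written | Threshold as written | Threshold from smallest size |
|---|---|---|---|
| 20% | 1.25/0.80 = 1.56-fold | 1.25 D0 | 1.000 D0 |
| 30% (minimum partial response) | 1.25/0.70 = 1.79-fold | 1.25 D0 | 0.875 D0 |
| 50% | 1.25/0.50 = 2.5-fold | 1.25 D0 | 0.625 D0 |
| 75% | 1.25/0.25 = 5-fold | 1.25 D0 | 0.3125 D0 |

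Once shrinkage exceeds 20% (1 − 1/1.25), a 25% regrowth from the smallest size is still below the reference diameter. The condition that the lesion exceed 1 cm applies throughout.

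**Example (assumed 40 mm reference, shrinking to 20 mm).** Partial response by size holds up to 0.70 × 40 = 28 mm, so regrowth from 20 to 28 mm (+40%) still meets partial response. Above 28 mm and below 1.25 × 40 = 50 mm it is stable disease. Measured from the smallest size, the threshold would be 1.25 × 20 = 25 mm.

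**Delay in time.** The documents give no growth rate. At an assumed 4 to 10 mm per month:
- 50% shrinkage: (50 − 25) = 25 mm, or 2.5 to 6.25 months.
- Minimum partial response: 40 to 28 mm, thresholds 50 and 35 mm, so 15 mm, or 1.5 to 3.75 months.

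These are delays for one patient, with no earlier call by another route. They are not shifts in a median and should not be set directly against the 6.9 and 7.1 month comparator medians in 3.4.3.

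**After a complete response (assumed 2 cm reference).** If reappearance is a new lesion, progression is at 1 cm. If it is regrowth, it is at 1.25 × 2 = 2.5 cm.

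**The case against.** Size is one route among several. A new lesion counts (7.1.4). The response table in 7.2 allows progression by any one component, including clear neurological worsening. Section 7.2 lets the investigator confirm a suspicious scan by PET, biopsy, repeat MRI or other means. Section 7.3 lets clinical status set TTP. A reader might infer that a responder who regrows cannot be progressive before 125% of the reference, or is classed as stable throughout. The documents do not support either reading: these routes can act earlier, and part of the regrowth is still partial response by size. What remains is that investigator confirmation is optional and the clinical routes depend on deterioration or judgement, so they do not repair the size criterion.

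The scope is narrow. Only responders with residual enhancement above 1 cm × 1 cm are affected, and no count is given. The earlier trial described in 3.4.3 enrolled patients after gross-total resection, so the group behind the reported complete responses may be small. This stands.

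The same rule applies to both randomised arms, so a difference between them needs unequal response rates. A reader might also infer that TTP is inflated against the historical cohorts. That depends on the progression reference those cohorts used, which the documents do not state. Both limits stand.

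Finally, section 9.2.3 notes that immune infiltration can cause cerebral edema, so a conservative size trigger backed by investigator judgement can be defended for treatment decisions. That does not settle how TTP should be dated.

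**Conclusion.** The point holds as a defect in the endpoint definition. The size criterion in 7.1.4 never resets after a response, so regrowth alone must reach 125% of the reference diameter: 1.79-fold after the minimum partial response and 2.5-fold after halving. Same-site reappearance after a complete response is unclassified. These statements rest only on the protocol's thresholds.

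The consequence for TTP is conditional. It can be lengthened selectively in responders. A bias between arms arises if response rates differ, and a bias against historical cohorts arises if they used a different reference. Any delay in months rests on an assumed growth rate. Section 10.3 says TTP is not primary and serves to derive hypotheses, so the primary analysis, sample size and power are unaffected. The change is worth making because the endpoint feeds a secondary objective and the judgement on daclizumab.

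**What to change.** In 7.1.4, for the TTP and progression-free survival endpoint:

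- Refer size progression to the smallest longest diameter recorded since and including the first post-radiation scan.
- State explicitly how enhancement reappearing at the same site after a complete response is classified for that endpoint.
- Keep the post-radiation scan as the reference for response.

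This takes a few sentences and no extra scans. The price is a somewhat shorter measured TTP and slightly more sensitivity to measurement error in small lesions, which the existing 1 cm condition limits.

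Vaccination continues until progression (5.2.1), and 7.2 continues protocol treatment until the investigator regards progression as documented. The sponsor must reconcile those passages with the endpoint definition. No rule for stopping treatment is proposed here.

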#### **7.1.5 Not Assessable**

Progression has not been documented and one or more sites have not been assessed.

## **7.2 Special Circumstances**

- **If a scan is suspicious but not definitive for progressive disease (including indeterminate lesion size or enhancement that is not clearly disease progression) in the absence of clinical progression, an investigator may elect to confirm progression through alternate means, including PET scan, biopsy, repeat MRI at 4 weeks, symptomatic follow up or other modalities.**
  - Protocol treatment will continue until the investigator considers progression documented.
- **Disease that was measurable at baseline and appeared to be one solid mass splits to become 2 or more smaller lesions**
  - note that the lesion has split, to identify the separate lesions as unique and to record the measurements of each.
  - appearance of these individual split lesions will not automate a response assignment of PD; they will contribute to a determination of progression only if the sum of all lesions meets the criteria for PD.
- **2 or more lesions which were distinctly separate at baseline become confluent at subsequent visits**
  - note the occurrence and capture the required measurement(s) of the confluent mass.
- **A required region of a baseline scan may be unavailable or technically inadequate, and 1 or more lesions are detected on a subsequent scans.**
  - Such lesions are identified as additional evaluable lesions that do not contribute to determination of that visit's response.
  - If at a successive time point disease progression is noted, the overall response per time point will be PD.
  - For those areas inadequate at baseline, the first scan available will become the reference scan by which later scans are compared for evaluable progression.
- **1 or more lesions are detected in regions unavailable or inadequate at baseline that were also not required**
  - regarded as new lesions, resulting in an overall response of PD for that time point.
- **Regions are not available or adequate at post-baseline visit assessments that showed disease at baseline**
  - an overall response of NA will be assigned to that visit unless other available data shows progression.

| Overall Response | Measurable Lesions                                                                    | Evaluable Lesions | New Lesions | Overall neurological status             | Steroid Use               | Additional notes                                                                                                 |
|-------------------------|----------------------------------------------------------------------------------------------|--------------------------|--------------------|------------------------------------------------|----------------------------------|-------------------------------------------------------------------------------------------------------------------------|
| PD               | PD                                                                                    | PD                | Yes         | Unequivocal worsening                   | Stable or increased use   | PD by any single component (not steroids by criteria) no sooner than 1 month after the first course of treatment |
| SD               | All other combinations, but please note the following particular combinations: |                          |                    |                                                |                                  |                                                                                                                         |
|                         | CR, PR or SD                                                                          | CR or SD          | No          | NA                                      | Off steroids, stable dose | Note that a lack of steroid or neurological information could prevent CR or PR from being recorded               |
|                         | CR, PR or SD                                                                          | CR or SD          | No          | improved, unchanged, possible worsening | NA                        | Note that a lack of steroid or neurological information could prevent CR or PR from being recorded               |
|                         | NA                                                                                    | NA                | NA          | improved, unchanged, possible worsening | Off steroids, stable use  |                                                                                                                         |
|                         | CR, PR or SD                                                                          | CR or SD          | No          | improved, unchanged, possible worsening | Off steroids, stable dose | A CR or PR overall response assignment is not possible with a neurological grading of -1.                        |
| PR               | PR or CR                                                                              | CR or SD          | No          | unchanged or improved                   | Off steroids, stable use  | All conditions need to apply and CR criteria do not apply.                                                       |
| CR               | CR                                                                                    | CR                | No          | unchanged or improved                   | Off steroids              | All conditions need to apply.                                                                                    |
| NA               | NA                                                                                    | NA                | NA          | NA                                      | Off steroids, stable dose | NA applies when NA is true of both radiology and neurological status.                                            |

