#### **7.1.1 Complete Response**

Complete disappearance of enhancing tumor on consecutive CT or MRI images at least 1 month apart, and neurologically stable or improved and at the same or a lower steroid dose. To be assigned a status of “Complete Response” as a best overall response, changes in tumor measurements must be confirmed by repeat assessments that should be performed no less than 4 weeks after the criteria for response is first met.

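### The overall-response table in Protocol 7.2 contradicts the protocol's own definitions on missing radiology and on steroid dose, and its last Stable Disease row overlaps its Complete and Partial Response rows

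*Protocol*

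**What the plan says.** Protocol 7.1 defines the response categories and 7.2 ends with a table that combines lesion, neurological and steroid findings into an overall response.

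**Missing radiology.** Section 7.1.5 defines Not Assessable as "Progression has not been documented and one or more sites have not been assessed", with no neurological condition. The last bullet of 7.2 covers regions that showed disease at baseline and are later unavailable or inadequate: "an overall response of NA will be assigned to that visit unless other available data shows progression". The table differs. One Stable Disease row has measurable, evaluable and new lesions all NA, steroids off or stable, and neurological status "improved, unchanged, possible worsening". The note on the NA row is "NA applies when NA is true of both radiology and neurological status".

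**Steroids.** Section 7.1.1 allows Complete Response if the patient is "neurologically stable or improved and at the same or a lower steroid dose", and 7.1.2 sets the same condition for Partial Response. In the table the Complete Response row lists only off steroids, with the note "All conditions need to apply". The Partial Response row lists off steroids or stable use, with the note "All conditions need to apply and CR criteria do not apply".

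**Remainder.** Stable Disease is the catch-all: "All other combinations, but please note the following particular combinations".

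**The concern.** The protocol fixes two incompatible rules for the same visit. An assessor who follows the table and one who follows the definitions will record different categories from identical data, and nothing says which governs.

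Two things are at stake. First, the count of complete and partial responses depends on the rule chosen, and Protocol 3.4.3 presents complete radiographic responses as prior evidence for this vaccine, so the counts will be read against that. Second, 7.3 defines time to progression by reference to these rules, and 2.2.2 lists progression-free survival against historical cohorts as a secondary objective. Under the table a visit at which the due scan was not done becomes a recorded non-progression, even where neurological worsening is judged possible.

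**Working it through.** The protocol states no figure to reproduce here. The check is to apply both rules to the same record.

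| Record | Table in 7.2 | Definitions in 7.1 and last bullet of 7.2 |
|---|---|---|
| All radiology NA, neurology unchanged, off steroids | Stable | Not Assessable |
| All radiology NA, possible worsening, stable steroids | Stable | Not Assessable |
| Complete disappearance, unchanged, stable dose | Partial (also meets last Stable row) | Complete |
| Complete disappearance, improved, lower non-zero dose | Stable (catch-all) | Complete |
| Partial shrinkage, improved, lower non-zero dose | Stable (catch-all) | Partial |
| Complete disappearance, improved, off steroids | Complete and last Stable row | Complete |
| Partial shrinkage, unchanged, stable dose | Partial and last Stable row | Partial |

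**All combinations.** Take 5 states for measurable lesions, 4 for evaluable lesions, 3 for new lesions, 5 for neurology and 5 for steroids (off, stable, lower, increased, missing): 5 × 4 × 3 × 5 × 5 = 1,500. Under both rules, any progression component counts as progression (1,020 combinations). Under the definitions, any missing radiology component without progression counts as Not Assessable. The other 480 divide as follows.

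- Some radiology missing: 4 × 3 × 2 = 24 non-progressing lesion patterns, of which 3 × 2 × 1 = 6 are complete, leaving 18. With 4 neurological and 5 steroid states, 18 × 4 × 5 = 360. The table calls 5 of these NA (everything missing) and the other 355 Stable; the definitions call all 360 Not Assessable. The explicit no-radiology row accounts for 3 × 2 = 6 of the 355. The rest reach Stable through the catch-all.
- Complete Response by 7.1.1: 6 combinations. The table gives 2 as Complete (off steroids), 2 as Partial (stable dose) and 2 as Stable (lower dose).
- Partial Response by the definitions: 18 combinations. The table gives 12 as Partial and 6 as Stable (lower non-zero dose).
- Stable under both: 96.

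Check: 360 + 6 + 18 + 96 = 480.

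**Overlap inside the table.** The rows for Complete (2 combinations) and Partial (2 + 12 = 14) cover 16. All 16 also satisfy the last Stable Disease row, because it lists improved and unchanged as well as possible worsening. The note beside that row bars a complete or partial response at a neurological grading of -1, so it appears meant for worsening only, but the row does not say so.

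These are counts of table cells, not patient frequencies.

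**Effect on time to progression.** A missed final scan scored Stable could add one scan interval of 4 to 12 weeks (from 8 ± 4) to a censored patient if censoring is at the last visit not scored as progression. An illustrative simulation compared that with censoring at the last imaged visit. Its assumptions are not in the protocol: exponential time to progression with median 28 or 64 weeks, scans every 4, 8 or 12 weeks, 10% or 30% of scans missed, and random loss to follow-up (mean 150 weeks) within 104 weeks. Mean added time per censored patient was 0.43 to 5.12 weeks, and the Kaplan-Meier median was the same under both rules in every setting.

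**The case against.** The strongest objection is that the consequences are limited. Section 10.3 says time to progression is not primary and is collected to generate hypotheses. Response rate is in neither objective list in 2.2. Section 7.1 applies to residual disease above 1 cm × 1 cm. Section 4.2.4 removes patients above physiologic steroid doses at first vaccination, which narrows the group affected by the steroid conflict, although later increases are allowed. A visit without a scan is not empty either: the no-radiology row requires a neurological assessment, and unequivocal worsening is progression by itself. All of this stands and limits the weight of the point. It does not make the rules agree.

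A reader might infer more: that the table inflates time to progression against the historical cohorts, and that a large share of vaccine visits is affected. The documents do not support that. They state no censoring rule, and one may sit in an analysis plan not shown. The flow sheet in Section 11 places MRI at even-numbered vaccines, so an odd-numbered vaccine visit has no scan due and is not a missed assessment. Later censoring of one patient is not a proportional shift in a median. If progression is found on a later scan, its date is the same whether the missed visit was Stable or Not Assessable, absent a missed-scan rule.

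A reader might also infer that the steroid wording in 7.1 must prevail. Nothing ranks it above the table. The Partial Response conflict also needs the dose to be reduced but not zero, and stable use to exclude a taper.

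**Conclusion.** The contradiction is certain on the current text and has three parts. A visit due for imaging with no radiology is Stable by the table and Not Assessable by 7.1.5 and the last bullet of 7.2. Complete disappearance on an unchanged steroid dose drops from Complete to Partial, and a complete or partial response on a reduced, non-zero dose drops to Stable. The last Stable row overlaps the Complete and Partial rows. The finding rests on reading the rows literally, with the catch-all applied as written.

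Importance is moderate. Response categories depend on the rule read, and a missed scan can be logged as non-progression. This can extend credited progression-free time in censored patients, but the protocol does not determine by how much.

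**What to change.** In the 7.2 table:

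1. Delete the Stable Disease row in which all radiology is NA. Reword the NA row so that Not Assessable applies when required radiology is missing and no other data show progression, as 7.1.5 and the last bullet of 7.2 already state. Exempt such visits from the Stable Disease catch-all.
2. Limit the neurological entry in the last Stable Disease row to possible worsening, so that it no longer overlaps the Complete and Partial Response rows.
3. Reconcile the steroid column with 7.1.1 and 7.1.2 so that one condition for each category stands in both places. Which condition applies is for the investigators to decide.

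The cost is an edit to one table, plus matching wording in 7.1.1 and 7.1.2 if the table's steroid condition is kept. There is no effect on sample size or visits. It should be done before responses are scored.
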